**Strengths and Limitations:**

The results of our study could help to better understand the OC behavior, may have implications for the development of effective immunotherapy and targeted pharmacological therapies for epithelial OC in a personalized medicine perspective. This will be a monocentric trial with an involvement of only 43 patients, so further studies will need to confirm our results.

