### Participants

2.2

Eligibility criteria are described in Table 1. The MICO study will enroll patients with advanced HGSO cancer.

**TABLE 1 cnr270242-tbl-0001:** MICO study inclusion and exclusion criteria.

Inclusion criteria	Exclusion criteria
Patients ≥ 18 and < 80 years old	Patients < 18 or > 80 years old
Pathologic diagnosis of HGSOC	Ongoing or suspended immunosuppressive therapy within the last 6 months
FIGO Stages III–IV	Congenital or acquired immunodeficiency
Patient having signed the consent to participate in the study	Immunosuppressive state
	BMI > 30
	Chemotherapy for another malignancy in the last 12 months
	Diagnosis of HGSOC without surgery

The control group will include women who underwent risk reduction bilateral salpingo‐oophorectomy and peritoneal biopsies due to genetic predisposition to OC. Exclusion criteria will be the same as for HGSO patients, excluding the diagnosis of HGSOC. Women with a diagnosis of occult peritoneal, ovarian, or tubal cancer and serous tubal intraepithelial carcinoma on definitive pathologic examination will also be excluded.

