### Sample Size

2.4

The sample size was calculated in order to evaluate the concordance between in vitro platinum‐based chemotherapy sensitivity and in vivo sensitivity.

From literature, this concordance is 0.80 with traditional patient‐derived xenografts [33]; we expect a concordance of 0.95 using PDOs [34]. A sample size of 93 patients will allow us to detect a true value of Cohen's Kappa of 0.95, with a power of 80% and an allocation of the two groups of 1:1.

Ninety‐three control patients will also be enrolled to compare the number of CD45+ cells at baseline. This sample size will allow estimating an effect size of CD45+ cell number of less than 0.3 between the control and case groups, with an alpha of 5% and power of 80%.

[32, 33].

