### Statistical Methods

2.11

The sample will be described in its characteristics using descriptive statistical techniques. Quantitative variables will be summarized with mean, standard deviation, minimum, and maximum. Qualitative variables will be described with frequency tables (absolute and percentages).

We will record platinum‐free interval, progression‐free survival, overall survival, and sensitivity to platinum‐based chemotherapy.

A univariate and multivariate Cox analysis will be implemented to explore factors associated with progression‐free survival. The proportional hazard assumption will be tested using the Schoenfeld residual test. Multivariable analysis will be corrected for potential confounding factors. Survival curves will be obtained using Kaplan–Meier analysis. All statistical tests will use a two‐tailed significance level of 0.05. The *χ*
^2^ test or Fisher's exact test will be used to analyze the distribution of variables according to different subgroups. The non‐parametric Wilcoxon test will be used to analyze the distribution of continuous variables.

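### With 93 cases and 93 controls the detectable standardised CD45+ difference is about 0.41, not below 0.3, and power at 0.3 is about 53% rather than 80%

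*Protocol article*

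**What the plan says.** Section 2.4 (Sample Size) first sizes the patient group for the primary concordance endpoint: "A sample size of 93 patients will allow us to detect a true value of Cohen's Kappa of 0.95". It then adds the same number of controls. Ninety-three "control patients will also be enrolled to compare the number of CD45+ cells at baseline", and of that number it says: "This sample size will allow estimating an effect size of CD45+ cell number of less than 0.3 between the control and case groups". Alpha is given as 5% and power as 80%. The type of effect size is not named.

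Three other places fix how the comparison works:

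- Section 2.2 (Participants) defines the controls as other women: "The control group will include women who underwent risk reduction bilateral salpingo‐oophorectomy and peritoneal biopsies due to genetic predisposition to OC". No matching or pairing with the patients is described.
- Section 2.11 (Statistical Methods) sets the sidedness: "All statistical tests will use a two‐tailed significance level of 0.05". For continuous measures it names the test: the non-parametric "Wilcoxon test will be used to analyze the distribution of continuous variables".
- Section 2.3 (Study Objectives and Endpoints) lists the comparison of the patients' tumour microenvironment with that of the controls among the secondary endpoints.

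**The concern.** The group sizes, alpha, power, sidedness and independence of the groups are all stated, so the detectable difference can be calculated directly. A standardised difference of 0.3 is small, and 80% power for it normally takes well over 100 subjects per group. Ninety-three per group therefore looked too few.

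This sentence is the only justification given for enrolling 93 control women. If it is wrong, the comparison is less sensitive than readers, and those who approved the control group, were told. A true difference of 0.3 SD would be missed nearly half the time instead of one time in five. A non-significant result could also be taken as evidence against differences that the study cannot reliably detect.

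**Working it through.** **Inputs.** n = 93 per group, alpha 0.05 and power 0.80 (Section 2.4); two-sided tests and the Wilcoxon test for continuous variables (Section 2.11); independent groups (Section 2.2). Assumption: the effect size is a standardised mean difference d, that is, a difference in SD units. The normal quantiles are 1.960 (two-sided 5%) and 0.842 (80% power), which sum to 2.802.

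**1. Attempt to reproduce the plan's figure.** The minimum detectable difference for two independent groups is

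d = (1.960 + 0.842) × √(2/93) = 2.802 × 0.1466 = **0.411**

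The exact t-test calculation gives 0.413. The stated value of less than 0.3 is not reproduced.

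**2. Power at d = 0.3 with 93 per group.** 0.3 / 0.1466 − 1.960 = 0.086, and Φ(0.086) = **0.534**. The t test gives 0.530.

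**3. Size needed for d = 0.3 at 80% power.** n = 2 × 2.802² / 0.3² = 174.4, so 175 per group. The t test gives 175.4, so **176** per group. The plan says *less than* 0.3, which needs more: at d = 0.25, 2 × 2.802² / 0.25² = 251.2, so 252 per group.

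**4. The Wilcoxon test.** With its asymptotic relative efficiency of 0.955, which holds under normality, the detectable difference is 0.411 / √0.955 = 0.42 and power at 0.3 is 51% to 52%.

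**5. Other readings that might recover a value below 0.3.**

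| Reading | Result at n = 93 (per group where there are two) | Fits the text? |
|---|---|---|
| One-sided 5% | d = 0.365 (t: 0.366); power at 0.3 about 65%; 138 per group for 80% (t: 138.1) | No. Still above 0.3, and tests are two-tailed |
| Paired or one-sample | 2.802 / √93 = 0.291 (t: 0.294) | No. Cases and controls are different women |
| 95% CI half-width | 1.96 × √(2/93) = 0.287 SD | No. The sentence states power |
| Cohen's f | 0.413 / 2 = 0.207 | Arithmetically true, but f is not named |
| Correlation r | 0.413 / √(0.413² + 4) = 0.202 | Arithmetically true, but r is not named |

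No calculation of a standardised mean difference between independent groups gives 80% power below 0.3 with 93 per group. The paired or one-sample formula comes just under 0.3 and may be where the figure came from. That is inference only, because the article gives no formula.

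**The case against.** The strongest objection is that the metric is assumed. The article says only *effect size*, and on the scale of Cohen's f or a correlation, 93 per group does detect a value below 0.3. The sentence also speaks of estimating, and the half-width of a 95% confidence interval is 0.287 SD. Neither reading fits well. The sentence compares a cell number between two groups, for which a standardised mean difference is the usual effect size, and nothing in the article points to f or r. Attaching 80% power makes it a statement about detection, not precision. What stands is that the metric has to be named; even on the favourable readings the sentence would mislead as written.

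Two narrower points also stand. The Wilcoxon figure depends on approximate normality; for other distributions the test can be more efficient than the t test, so 0.42 is a guide only. And Section 2.11 names the Wilcoxon test for continuous variables in general, without tying it to this comparison.

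On importance, the comparison is secondary, the article gives no reason why 0.3 matters, and it plans no conclusion of equivalence. The risk that a null result is over-read is therefore a possibility, not something the plan commits to. This limits the consequences but does not make the figure correct.

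**Conclusion.** The concern holds. For two independent groups of 93, two-sided 5% and 80% power, the detectable standardised difference is about 0.41, roughly 40% larger than the 0.3 given as an upper limit (0.411 / 0.3 = 1.37). Power at 0.3 is about 53%, some 27 percentage points below the 80% stated. This rests on one assumption, that the effect size is a standardised mean difference; the other inputs come from the article. The kappa calculation for the primary endpoint does not depend on it.

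The calculation takes the 93 in Section 2.4 at face value. The abstract gives a different number of patients: "This will be a monocentric trial with an involvement of only 43 patients". That conflict is a separate point. If the true figure were 43 in each group (the number of controls being an assumption), the detectable difference would be about 0.61 and power at 0.3 about 28%.

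**What to change.** Name the effect-size metric and the test in Section 2.4, and replace the claim with wording such as:

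*With 93 cases and 93 controls, a two-sided test at the 5% level has 80% power to detect a standardised mean difference in CD45+ cell number of 0.41 (about 0.42 with the Wilcoxon test, assuming approximate normality). Power for a difference of 0.3 is about 53%.*

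This changes one sentence, enrols no one extra and leaves the primary endpoint alone. The only cost is a less favourable stated sensitivity. If the sponsor instead needs 80% power at 0.3, the size must change, to about 176 per group with a t test and somewhat more with the Wilcoxon test (174.4 / 0.955 = 182.6, so about 183). If a different metric was meant, the sentence should say so and give the equivalent difference in SD units.

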### Blood Samples

2.5

Blood samples are collected before the surgery and peripheral blood mononucleated cells (PBMCs) are isolated using Ficoll Paque Plus (GE Healthcare Pharmacia, Cat No: 17‐1440‐03) and SepMate 50 mL Tubes (Stem Cell Technologies, Cat No: 154500) following the manufacturer's instructions. The supernatant is thoroughly discarded, the pellet is resuspended in 1 mL of Bambanker (NIPPON Genetics Europe GmbH, Cat No: BB02), and stored at −80°C.

### Patient Tissue Sample Manipulation

2.6

Biopsies from patients with FIGO stages III–IV HGSOC will be collected from patients treated at the Obstetrics‐Gynecology Department of Ospedale Santa Maria della Misericordia, Udine, Italy. HGSOC tissue samples are gently washed with PBS in a 60 mm Petri dish (Corning, Cat. No: 430166) to remove excess blood, and then moved to a new Petri dish with AdDF^+++^ culture medium (Advanced DMEM/F12 (ThermoFisher, Cat. No: 12634010) containing L‐Glutamine (Merck, Cat. No: G7513‐100ML), 10 mM HEPES (Merck, Cat. No: 63264‐100ML‐F) and Penicillin–Streptomycin (Life Technologies, Cat. No: 15070063). Tissue is then minced with a scalpel into small fragments of 1–2 mm^2^ and digested in 5 mL AdDF+++ containing 5 μM RHO/ROCK pathway inhibitor (Y‐27632, Tocris) and 100 μg/mL Primocin (Invivogen, Cat. No: ant‐pm‐1), 1 mg/mL Collagenase type IV (ThermoFisher, Cat. No: 17104019) on an orbital shaker at 37°C for 1 h 30 min.

The cell suspension is then filtered through a 100uM Cell Strainer (Starlab, Cat. No: CC8111‐0072) placed on a 50 mL tube and washed with 5‐10 mL of AdDF^+++^ culture medium and centrifuged at 1200 rpm for 5 min at room temperature. The pellet is resuspended with AdDF^+++^ and cells, diluted in 1× Trypan Blue (Sigma‐Aldrich, Cat. No: T6154), are counted using a Neubauer chamber. Cells are used for cytofluorimetric analyses and organoid generation.

### Patient‐Derived Organoid Generation and Characterization

2.7

For organoid generation, 30,000 cells/well of a pre‐warmed 24‐well (Greiner, Cat. No: 662160) are embedded in a mix of 1/3 of AdDF^+++^ culture medium and 2/3 Matrigel (Corning, Cat. No: 356231). The plate is placed at 37°C for 20 min to allow the Matrigel to polymerize before being overlaid with 500uL of complete growth factor medium and incubated at 37°C.

Complete growth factor medium consists of AdDF^+++^ culture medium supplemented with 100 ng/mL recombinant mEGF (ThermoFisher, Cat. No: 315‐09‐1 mg), 0.5uM A83‐01 (Tocris, Cat. No: 2939), 1 mM Nicotinamide (Sigma‐Aldrich, Cat. No: N0636), 1× N2 supplement (Life Technologies, Cat. No: 17502048), 1× B27 Supplement (Life Technologies, Cat. No: 17504044).

For cryopreservation of the cells, resuspend the pellet in the appropriate volume of a mix composed of 60% AdDF^+++^, 30% FBS, and 10% DMSO (AppliChem, Cat. No: APA36720250). The mutational profile of the PDOs, which may include mutations in BRCA1, BRCA2, TP53, and so on, will be evaluated using the Sanger method and subsequently compared with those of the parental tumor tissue.

### Organoids Viability Assay

2.8

Organoids will be released from Matrigel by using Cell Recovery Solution (Corning) and collected by centrifugation. Organoid pellet was combined with Matrigel in a 1–2 ratio and seeded in a 96‐well plate at 20 μL per well. After Matrigel solidification 80 μL of complete medium is added. Carboplatin) will be added 2 two days after embedding, and cell viability will be measured after 5 days using Cell Titer‐Glo (Promega) following manufacturers' indications. Data will be analyzed with GraphPad Prism 9.0 software to calculate IC_50_.

For co‐culture experiments, B cells are isolated from peripheral blood using the B cell isolation kit (Milteny) and 100,000 cells will be added to each 96‐well containing organoids before drugs addiction. Similarly, for PDO and mast cell co‐cultures, 100,000 cells of the human mast cell line HMC‐1 or LAD2 will be used.

### Flowcytometry

2.9

For flow cytometry analysis of B lymphocytes and MC in HGSOC samples, frozen cells are rapidly defrosted in PBS + 2% FBS + 5 mM EDTA (FACS buffer), centrifuged at 1200 rpm for 5 min at room temperature, and stained for 25 min at 4°C in the dark with monoclonal fluorescent conjugated antibodies plus Fixable Viability Dye eFluor 780 (listed in Tables 2, 3, 4), following the manufacturer's instructions. Cells are then washed with 2 mL of FACS Buffer, centrifuged at 1200 rpm for 5 min at room temperature, resuspended in 500uL of FACS Buffer, and acquired with Attune NxT flow cytometer.

**TABLE 2 cnr270242-tbl-0002:** List of the antibodies used for flow cytometry analysis of B, T cells, and mast cells, within the TME.

Target	Fluorophore	Clone
CD3	FITC	UCHT1
CD19	eFluor 450	SJ25C1
CD45	PE‐AlexaFluor 610	HI30
CD117 (c‐kit)	APC	104D2
FcεRI	SB600	AER‐37 (CRA1)
Fixable viability dye	eFluor 780	From Invitrogen

**TABLE 3 cnr270242-tbl-0003:** List of the antibodies used for flow cytometry analysis of B lymphocytes within the TME.

Target	Fluorophore	Clone
CD19	APC	HIB19
CD20	Brilliant Violet 510	2H7
CD24	PE/Dazzle 594	ML5
CD27	PE/Cy7	O323
IgM	PerCP‐Cy5.5	MHM‐88
CD38	Brilliant Violet 421	HIT2
CD45	FITC	HI30
CD21	SB600	HB5
IgD	SB702	IA6‐2
Fixable viability dye	eFluor 780	From Invitrogen

**TABLE 4 cnr270242-tbl-0004:** List of the antibodies used for flow cytometry analysis of circulating B lymphocytes.

Target	Fluorophore	Clone
CD19	APC	HIB19
CD20	Brilliant Violet 510	2H7
CD24	PE/Dazzle 594	ML5
CD27	PE/Cy7	O323
IgM	PerCP‐Cy5.5	MHM‐88
CD38	Brilliant Violet 421	HIT2
CD71	FITC	OKT‐9
IgD	SB702	IA6‐2
Fixable viability dye	eFluor 780	From Invitrogen

Flowcytometry analysis has been performed with FlowJo software.

### Histopathology and Immunofluorescence

2.10

Biopsy tumor tissue will be fixed in 4% paraformaldehyde, dehydrated, and embedded in paraffin. After antigen removal, sections will be cut. Two biopsy specimens are used for histological examination. and the others will be used for in vitro experiments. The following antibodies will be used: anti‐human CD4, anti‐human CD8, anti‐human CD20 (Dako, Glostrup, Denmark), anti‐human mast cell tryptase (Dako). Aminoethylcarbazole (Dako) is used as a chromogenic substrate. Slides will be evaluated under a Leica DM3000 optical microscope, and microphotographs will be collected with a Leica DFC320 digital camera (Leica, Wetzlar, Germany). All cells will be detected and counted out of 5 × 40 high‐power microscopic fields in each case. For double‐marker immunofluorescence, sections will undergo 2 sequential rounds of single‐marker immunostaining. The following antibodies will be used: anti‐human tryptase, anti‐human TNF‐a, anti‐human IL‐17, anti‐human IL‐10 (all from ThermoFisher) and Alexa Fluor 488– and Alexa Fluor 568–conjugated specific secondary antibodies. Fluorescent images will be collected using a laser scanning confocal microscope (LEICA TCS SP8, Leica Microsystems).

For immunofluorescence analysis of PDO, organoids will be seeded on ibiTreat μ‐Slide 8 wells chambered coverslip (Ibidi) and fixed with 4% PFA (paraformaldehyde) for 20 min at RT. Then wells will be incubated for 20 min with NH_4_Cl at room temperature. Organoids will be permeabilized with PBS + TritonX‐100 0.5% for 10 min at RT, blocked for at least 1 h in PBS + 1% FBS, stained ON with primary antibody and with secondary antibody for 2 h in blocking buffer. The following antibodies will be used: anti‐CK7, anti‐PAX8, anti‐WT‐1 (all from ThermoFisher). Mounting media containing DAPI will be used to stain nuclei.

### Statistical Methods

2.11

The sample will be described in its characteristics using descriptive statistical techniques. Quantitative variables will be summarized with mean, standard deviation, minimum, and maximum. Qualitative variables will be described with frequency tables (absolute and percentages).

We will record platinum‐free interval, progression‐free survival, overall survival, and sensitivity to platinum‐based chemotherapy.

A univariate and multivariate Cox analysis will be implemented to explore factors associated with progression‐free survival. The proportional hazard assumption will be tested using the Schoenfeld residual test. Multivariable analysis will be corrected for potential confounding factors. Survival curves will be obtained using Kaplan–Meier analysis. All statistical tests will use a two‐tailed significance level of 0.05. The *χ*
^2^ test or Fisher's exact test will be used to analyze the distribution of variables according to different subgroups. The non‐parametric Wilcoxon test will be used to analyze the distribution of continuous variables.

## Discussion

3

The knowledge of TME, integrated with genetic and molecular features, could help to better understand the OC behavior. In recent decades, considerable effort has been dedicated to understanding the role of immune cells in OC, with particular attention paid to T cells and macrophages. However, therapies targeting T cells (such as those which act on the PD1, LAG3 or TIGIT pathways) have yielded limited success in OC so far [35] suggesting that other immune cells or other pathways might play a pivotal role in this type of tumor.

Among cells under investigation, B cells and mast cells could represent putative crucial cells able to influence the TME. Beyond their antibody‐mediated functions, B cells can act as antigen‐presenting cells influencing T cell activation, can interact with innate immune cells modulating the immune responses in both beneficial and detrimental ways, and can produce mediators with inflammatory or immunosuppressive functions [36].

Similarly, a growing body of literature supports the key role of mast cells, primarily well known for their role in IgE‐mediated allergic response, in tumor progression in a variety of cancers, making them a highly attractive therapeutic target for a wide range of malignancies [37]. However, the data available in the context of gynecological malignancies are mostly controversial, sustaining both pro‐tumoral [38] and anti‐tumoral effect of mast cell on OC [17].

For these reasons, the MICO project aims to identify the main populations of immune cells in the TME and characterize in detail the role of B and mast cells in HGSOC patients by monitoring their accumulation and their phenotype among different patients, in relation to disease progression (FIGO stage) and in response to NACT. In parallel, PDO co‐cultures will be used as an in vitro model to study the effects of B lymphocytes and mast cells on cell growth and drug response. The in vitro data will be compared with patient response to therapy. This information could have both prognostic and therapeutic relevance. Some patients may have tumors with specific TME features that may influence the aggressiveness or treatment response of the tumor itself. From a personalized medicine perspective, the better knowledge of TME could tailor the treatment and management of OC to the unique characteristics of the specific patient's tumor.

Analyses of immunophenotype will assist physicians in identifying those eligible for targeted pharmacological therapies and/or early immunotherapy. Personalized treatment plans will involve combinations of therapies to target both the tumor and its microenvironment.

TME is not static [39]; it can change over time, affecting the tumor's response to treatment. Personalized medicine involves monitoring these changes and adapting the treatment plan as needed. Understanding and targeting the TME is an essential aspect of tailoring cancer treatment to the individual patient's needs and optimizing treatment outcomes. In the future, the results of our study may have implications for the development of effective immunotherapy of epithelial OC, an immunogenic disease currently resistant to checkpoint inhibitors.

A limit of our study might be the heterogeneity of TME in OC and the small size of peritoneal biopsies. To overcome this, biopsies will be collected by an experienced gynecologic oncology surgeon and will be collected where carcinosis will be most represented. If the results in our study are promising, to increase the number of patients and overcome the possible heterogeneity of OC, we will design a multicenter study to validate the results in different populations.

## Conclusions

4

In this prospective study, we will analyze the association between the composition of the TME, the reactivity of patient‐derived organoids, and patients' clinical data to determine if specific subpopulations of tumor‐infiltrating immune cells can predict epithelial OC outcomes. By comparing molecular profiles, in vitro drug responses, and clinical‐pathological data, we aim to identify patterns that can predict the primary tumor's response and identify patients who may benefit from specific treatments. In the future, our study's results may contribute to developing effective immunotherapy for OC.

## Ethics Statement

This study and all its methods will be carried out in accordance with the ethical standards of the institution and the National Commission for Human Experimentation, as well as the 1964 Declaration of Helsinki and its subsequent amendments or equivalent. This trial has received ethical approval by the Friuli Venezia Giulia Ethics Committee (CEUR FVG) of the Regional Health Institute with ID protocol n. 17 380, in October 2023. This committee is independent and not related to any affiliation of the authors. Any subsequent will of modification of the protocol would be submitted to the agreement of the committee. The clinical trial has been registered Clinical‐Trials.gov with the identifier NCT06272240.

